### Testing

Data collection will occur prior to, directly after and at one, two and five years following the completion of the 16-week intervention period as shown in Fig. 1. The primary outcome is fatigue. Secondary outcomes are return to work, muscle strength and function, cardiovascular fitness, systemic inflammation, mitochondrial density, muscle fibre area, QoL, pain, disease status and treatment-related symptoms.

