## Statistical analyses

Data will be analysed using the IBM SPSS (Statistical Package for the Social Sciences) 20 statistical package for Windows (SPSS, Chicago, IL, USA). Analyses will include standard descriptive statistics (one-way ANOVAs or Kruskall-Wallis tests, as appropriate, and Chi squared tests). ANCOVAs accounting for baseline values will be used for the main analysis. Variables with data that are not normally-distributed will be log transformed prior to ANCOVA analyses. Paired t-tests or Wilcoxon signed rank tests, as appropriate, will be used to test for within groups differences from baseline to follow up. All tests will be 2-tailed and statistical significance set at *p* ≤ 0.05. An intention-to-treat approach will be used for the analyses with missing values replaced using the expectation-maximization method.

Power Calculation: With fatigue as the primary outcome measure, a sample size of 65 patients/group is required, based on an effect size of 0.53 and power = 0.8. From our research group’s experience with participant dropout in previous exercise trials in cancer survivors, we accounted for an attrition rate of ~20% and therefore are aiming to recruit 80 participants into each group.

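### Filling missing outcomes once by expectation-maximization and running the ANCOVA on the completed data gives either standard errors that are too small or a diluted effect

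*Protocol article*

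**What the plan says.** Everything on this point is in the protocol article, mostly under Statistical analyses.

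- Main model: "ANCOVAs accounting for baseline values will be used for the main analysis".
- Missing data: "An intention-to-treat approach will be used for the analyses with missing values replaced using the expectation-maximization method".
- Testing: "All tests will be 2-tailed and statistical significance set at" p ≤ 0.05.
- Power Calculation: "a sample size of 65 patients/group is required, based on an effect size of 0.53 and power = 0.8". For dropout, "we accounted for an attrition rate of ~20"%, hence "aiming to recruit 80 participants into each group".
- Visits (Testing section): "Data collection will occur prior to, directly after and at one, two and five years following the completion of the 16-week intervention period".

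The section mentions no repeated draws, pooling or variance correction, and does not say whether arm enters the imputation model. The replacement rule is not limited to one outcome or visit.

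**The concern.** An expectation-maximization fill replaces a missing score with a value predicted from the observed data. An ANCOVA run on the completed data cannot tell predictions from measurements, so it counts all 80 women per arm as observed when only about 64 (80 × 0.80) would have supplied an outcome. The plan is at odds with itself here: the power calculation treats dropouts as lost information and recruits extra women to make up for them, and the analysis rule then puts the dropouts back as data.

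What goes wrong depends on a choice the protocol leaves open. With arm in the imputation model, the estimate is right but its precision is overstated. With arm left out, imputed women are pulled to a regression line common to all arms and the arm difference shrinks. The primary fatigue comparison is exposed either way. The rule also reaches the 1, 2 and 5 year visits, where missingness may well be higher (an inference, not a stated figure). The trial follows survival, and nothing in the rule exempts visits after a death, so read literally it would assign fatigue scores to women who have died.

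**Working it through.** **Inputs from the protocol.** Three arms at 1:1:1, 80 per arm; two-sided 0.05; effect size 0.53; attrition about 20%; ANCOVA on baseline.

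**Assumed, not in the protocol.** Baseline-outcome correlation ρ = 0.5 (range 0.3 to 0.7); missing fraction m from 10% to 30% around the planned 20%; missing completely at random, or dependent on baseline.

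**The plan's own figures.** 2(1.960 + 0.842)² / 0.53² = 55.9, so 56 per group (57 by t-test), not 65; 65 corresponds to about 85% power. 65/0.80 = 81.25, so 82 against 80 recruited; 65/80 implies 18.75% attrition. The mismatch at 65 is a separate matter, and nothing below depends on it. The attrition allowance is consistent with about 20%.

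**Arm in the imputation model.** Let σ² be the residual variance and n the number randomised per arm.

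- True variance of an arm difference: 2σ² / (n(1−m)), because only n(1−m) women per arm carry information.
- Reported variance: the filled points have zero residual, so residual variance is estimated as about σ²(1−m) and divided by the full n, giving 2σ²(1−m) / n.
- Ratio of reported to true standard error: 1−m.

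With ρ = 0.5, σ² = 0.75. True SE = √(1.5/64) = 0.153; reported SE = √(1.2/80) = 0.122; ratio 0.80. Type I error = 2[1 − Φ(1.96 × 0.80)] = 0.117.

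Simulation (6,000 runs per scenario, ρ = 0.5 unless stated):

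| Missing | Reported SE / true SE | Pairwise type I error | Three-group F-test |
|---|---|---|---|
| 10% | 0.89 | 0.080 | 0.091 |
| 20% | 0.79 | 0.117 | 0.147 |
| 30% | 0.70 | 0.173 | 0.238 |
| 20%, ρ = 0.3 | 0.80 | 0.116 | 0.148 |
| 20%, ρ = 0.7 | 0.80 | 0.114 | 0.148 |
| 20%, dependent on baseline | 0.77 | 0.130 | 0.174 |

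**Arm not in the imputation model.** Imputed women contribute essentially no arm difference, so the expected estimate is about 0.53(1−m): 0.477, 0.424 and 0.371 at 10%, 20% and 30%. Simulated: 0.476, 0.422 and 0.371 (0.411 at 20% with baseline-dependent missingness). Type I error is 0.048 at 20%, and power is unchanged (0.926 against 0.928 on observed data). Intervals are centred in the wrong place: the bias is (0.53 − 0.422)/0.123 = 0.88 standard errors, so a 95% interval covers the true effect with probability about Φ(1.08) − Φ(−2.84) = 0.86.

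**One random draw instead of a predicted mean, arm in the model.** True variance is 1/(1−m) + m = 1.25 + 0.20 = 1.45 times the reported one. Type I error = 2[1 − Φ(1.96/√1.45)] = 0.104.

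**Comparator.** Baseline-adjusted ANCOVA on observed outcomes, 20% missing: estimate 0.53, reported SE 0.154 against true 0.154, pairwise type I error 0.046, power 0.93 (0.87 to 0.99 for ρ from 0.3 to 0.7).

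**The case against.** The strongest reply is that the text says less than the criticism assumes. It does not state that the fill is done once, does not exclude residual draws or pooling, and does not give the imputation model; a journal article may leave such detail elsewhere. That is fair as far as it goes, and the single fill is an inference. But it is the plain reading of replacing values before an ANCOVA, and the method itself is stated, not left open.

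Second, the two harms exclude each other, and with arm left out the test under the null is valid. This stands. It is therefore too strong to say that the p-values are invalid under every reading; in that branch the fault is a biased effect size with an interval in the wrong place.

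Third, the fill could use other measured variables, which would reduce the error. It would. If an auxiliary variable explains a share s of the residual variance and is observed for everyone, the ratio of reported to true variance becomes (1 − m(1−s)) / ((1−s)/(1−m) + s). At m = 0.20 this is 0.85/1.1875 = 0.716 for s = 0.25 and 0.90/1.125 = 0.80 for s = 0.50, giving type I errors of about 10% and 8%. The error is smaller but still above 5%, and women lost entirely after baseline have no such follow-up data to draw on.

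Fourth, the 20% is a recruitment allowance not tied to the 16-week visit, and the handling of deaths is normally analysis-plan detail. Both are reasonable. Even 10% missing gives a pairwise error of 8%, and the main point does not depend on the deaths.

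**Conclusion.** The concern holds. As worded, the missing-data rule cannot give both an unbiased arm difference and a valid test. At the plan's own 20%, either the standard error is about a fifth too small and the pairwise type I error more than doubles to about 12% (about 15% for the F-test), or a 0.53 SD effect is reported as about 0.42. A single random draw still gives about 10%.

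This rests on reading the rule as a single fill, and on a missing fraction near the planned attrition. The assumed correlation hardly matters, and completely random missingness is the lenient case when arm is in the model. Useful auxiliary data would bring that error down to roughly 8% to 10%. Because the rule governs the primary outcome, it should be changed before any analysis.

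**What to change.** Delete the expectation-maximization replacement and state one of the following:

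- a likelihood-based mixed model for repeated measures on observed data, with arm, visit (16 weeks, 1, 2 and 5 years), arm × visit, baseline and baseline × visit, including every randomised woman with at least one post-baseline value; or
- multiple imputation with arm, baseline and the other visits in the imputation model, followed by the planned ANCOVA and pooling by Rubin's rules.

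State that scores are not imputed after death. Add one sensitivity analysis for the 16-week primary comparison in which missing values are shifted by a fixed amount, to test departure from missing at random. This is a desirable addition and is not needed to cure the main fault.

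The cost is a revision of the analysis section, submitted as an amendment as the protocol's Ethics section requires. No new data or extra patients are needed. Compared with a fill that includes arm, confidence intervals widen to their correct length: the standard error at 20% missing goes from 0.122 to about 0.154. Pairwise power at 0.53 SD is still about 0.93 under the assumed correlation of 0.5, for a single comparison at 0.05.

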The primary aim of the study is to compare the effects of two different exercise regimens (aerobic exercise vs. a combination of aerobic and resistance exercise) and a usual care control group on the primary outcome cancer related fatigue and the secondary outcomes cardiovascular fitness, muscle strength, function and structure, systemic inflammation, gene activity, health related quality of life, pain, disease and treatment related symptoms in patients with breast cancer receiving chemotherapy. The second aim is to examine if these effects, if any, are sustained one, two, and five years following the completion of the intervention and to monitor the effects of the intervention on return to work, recurrence and survival. The third aim of the study is to examine the effect of attendance and adherence rates on the effects of the exercise programme.

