### Randomisation process

The participants are randomly allocated by the Clinical Studies Unit at Radiumhemmet, Karolinska University Hospital (Stockholm, Sweden) to either AT, CT, or UC at a 1:1:1 ratio using a computer-generated program. A randomly selected subset of participants (*n* = 45) will also undergo a muscle biopsy before and after the intervention.

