## Intervention

### Phase I: Initial intervention- Supervised exercise training

Participants in the exercise groups begin training the week after the initial testing session which takes place prior to the patients’ second session of chemotherapy. Both exercise groups train twice per week on non-consecutive week days for 16 weeks. Each session is approximately 60 min in duration and is conducted at the exercise clinic at the Karolinska University Hospital. An exercise physiologist or oncology nurse supervises all sessions to ensure safety, correct technique and adherence to the exercise protocols. Participants can choose to perform the continuous aerobic exercise on a cycle ergometer, elliptical ergometer, or treadmill, the interval aerobic exercise is performed on a cycle ergometer. Resistance exercises are performed using machine resistance training equipment, participants’ body weight and free weight dumbbells and barbells. All exercise sessions commence with a five min warm up on a cycle ergometer, treadmill, or rowing machine at a rating of perceived exertion (RPE) of 10–12 on the Borg scale [34] and sessions conclude with a 10 min cool-down which includes dynamic and static muscle stretching activities of the major muscle groups.

Group 1 (AT) exercise sessions commence with 20 min of moderate intensity continuous aerobic exercise at an RPE of 13–15. This is followed by 3 × 3 min bouts of high intensity intermittent aerobic exercise at an RPE of 16–18 interspersed with ~1 min of passive or active recovery.

Group 2 (CT) completes both resistance exercises and high intensity intermittent aerobic exercise during each session. The resistance training regimen consists of 8 exercises (leg press, biceps curls, triceps extensions, bench press, shoulder press, standing row, sit ups/Russian weighted abdominal twist, and prone lying back extensions. Participants complete 2 sets of 8–12 repetitions at an initial intensity of 70% of their estimated 1 repetition maximum (1-RM) strength, and increase to 80% of estimated 1-RM when more than 12 repetitions can be correctly performed by the participant. Every four weeks estimated 1-RM strength tests are performed to ensure progression. Group 2 also completes 3 × 3 min bouts of high intensity intermittent aerobic exercise (RPE = 16–18) interspersed with ~1 min of passive or active recovery.

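### The stated 65 per group does not follow from effect size 0.53, 80% power and a two-sided 5% level: those inputs need 57, and 65 gives 85% power

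*Protocol article*

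**What the plan says.** Statistical analyses, Power Calculation, gives fatigue as the primary outcome and states that "a sample size of 65 patients/group is required, based on an effect size of 0.53 and power = 0.8". It then allows for attrition of about 20%, and the authors "therefore are aiming to recruit 80 participants into each group".

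The paragraph names no alpha, test or contrast of its own. The level comes from the paragraph before it: "All tests will be 2-tailed and statistical significance set at" p ≤ 0.05. That paragraph also makes ANCOVA adjusted for baseline the main analysis.

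Participants are allocated "to either AT, CT, or UC at a 1:1:1 ratio using a computer-generated program" (Randomisation process). The primary aim, at the end of the Background, covers all three arms: "compare the effects of two different exercise regimens (aerobic exercise vs. a combination of aerobic and resistance exercise) and a usual care control group". Fatigue is the primary outcome there too. One sample-size figure therefore stands for a three-arm question.

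**The concern.** The article prints sample size, effect size, power, significance level and sidedness together, so the sentence can be checked against itself. It fails that check by 8 patients per group, which is more than rounding or the choice between a normal and a t calculation explains.

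The trial rests on this figure for its primary outcome. As printed, a reader cannot tell whether the trial has more power than claimed for one comparison, or whether 65 reflects an allowance for several comparisons that was never stated. The two cases lead to different statements of power. The second also bears on how a non-significant difference between the two exercise arms should be read.

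**Working it through.** **Inputs.** All are from the Protocol article.
- Effect size d = 0.53, power 0.80, n = 65 per group, about 20% attrition, 80 recruited per group (Power Calculation).
- Two-sided alpha 0.05 (Statistical analyses).
- Three arms, 1:1:1 (Randomisation process).
- Assumption: 0.53 is a difference in means divided by the SD. The article does not define it.

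**Step 1. Try to reproduce 65.** Normal approximation for two equal groups:

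n = 2 × [(z₀.₉₇₅ + z₀.₈₀) / d]² = 2 × [(1.960 + 0.842) / 0.53]² = 55.9, so 56 per group.

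The exact noncentral-t calculation gives 57 per group (power 80.1% at 57, 79.4% at 56). Neither gives 65.

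**Step 2. Power at the stated size.** The noncentrality is d × √(n/2).
- n = 65: 0.53 × √32.5 = 3.021. Exact t power is 85.1% (85.6% by normal approximation).
- n = 64, from 80 × 0.80: 0.53 × √32 = 2.998. Exact t power is 84.5%.

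By exact t, 65 is the size needed for 85% power, not 80%.

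**Step 3. Could an unstated rule lie behind 65?** The article states none of the rules below. All use d = 0.53 with no gain from the baseline covariate.

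| Rule | n per group for 80% | Power at 65 |
|---|---|---|
| Two-sided 0.05, one pair | 57 | 85.1% |
| One-sided 0.05 | 45 | 91.3% |
| Dunnett, two arms against control | 67–68 | 78.5–79.1% |
| Alpha 0.025 (Bonferroni, two pairs) | 69 | 77.3% |
| Alpha 0.0167 (Bonferroni, three pairs) | 76 | 72.4% |
| Omnibus F, one arm midway | 70 | 77.0% |
| Omnibus F, two arms equal | 53 | 88.3% |

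By normal approximation, the two-sided alpha at which 65 per group gives 80% power is about 0.029, which is none of the levels above.

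**Step 4. Effect of ANCOVA.** If 0.53 is on the unadjusted SD scale and baseline and follow-up correlate at r, the effective d is 0.53 / √(1 − r²). The article gives no r, so these values are assumed.

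| r | Effective d | Power at 65, alpha 0.0167 | n for 80%, alpha 0.0167 | n for 80%, alpha 0.05 |
|---|---|---|---|---|
| 0.3 | 0.556 | 77% | 70 | 52 |
| 0.4 | 0.578 | 81% | 65 | 48 |
| 0.5 | 0.612 | 85% | 58 | 43 |

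So r near 0.4 does reproduce 65 at alpha 0.0167. At the stated 5% level, any positive r moves the required size further below 65.

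**Step 5. What any one pair can show.** With 64 per group, two-sided 5% and no covariate gain, 80% power is reached at d = 0.50. The 95% CI half-width is 1.979 × √(2/64) = 0.35 SD.

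**The case against.** The strongest reply is that *does not reproduce* means only *not under a plain t-test*. The main analysis is ANCOVA, the trial has three arms, and the test and contrast behind 65 are not given. A baseline correlation of about 0.4 with a three-pair Bonferroni level gives 65. Dunnett against control comes close at 67–68, and a worst-case efficiency allowance for a rank test gives 65–66. This stands to the extent that 65 may have had a coherent origin, and it would be wrong to say that no three-arm design fits it. It does not rescue the printed sentence. The only stated level is 5%, and at that level ANCOVA widens the gap.

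A second reply is that the multiplicity rule and the order of contrasts may sit in an analysis plan that is not shown. That is fair, and their absence is not the point here. The point is that the printed figures disagree with each other.

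Three stronger readings are tempting, and the article does not support them.
- *The trial has only 72% power.* That needs Bonferroni over three pairs and no baseline correlation. The plan adopts no such adjustment, and it does adjust for baseline.
- *Recruitment is short, because 80 × 0.80 = 64.* Attrition is given as about 20%. A loss from 80 to 65 is 18.75%, and one patient per group costs 0.6 points of power.
- *The aerobic-versus-combined comparison is badly underpowered.* The arms do share an element ("Group 2 also completes 3 × 3 min bouts of high intensity intermittent aerobic exercise"), but they also differ: continuous aerobic work in one, eight resistance exercises in the other. The article does not say which contrast 0.53 refers to or what difference is expected between the exercise arms. Nor does it say that a null result will be read as equivalence. Only a caution about interpretation remains.

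**Conclusion.** The concern holds as an internal inconsistency in the power statement. At the article's only stated level, 80% power needs 57 per group, and 65 gives 85% (84.5% at 64). This rests on reading 0.53 as a standardised mean difference and on a single two-group comparison without covariate gain.

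On that reading the error is conservative: the trial is larger than its stated power requires, and the recruitment target is not in question. If an adjustment for three arms was intended, the sentence misleads because it does not say so. The power at 65 would then range from about 72% to 79% under the pairwise adjustments tabulated, before any gain from the baseline covariate. Those figures are conditional on rules that the article does not adopt.

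The point is worth correcting because it concerns the primary outcome, can be verified from the printed figures and is cheap to put right. It does not undermine the design.

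**What to change.** Keep 80 per arm and rewrite the power paragraph so that it does the following.
- It names the contrast, the two-sided alpha and the test behind the figure, and says what 0.53 measures.
- It gives the matching power. For one unadjusted comparison at two-sided 5%, that is 57 per group for 80%, or about 85% with 64–65 per group. If an adjustment for several comparisons is adopted, it gives the lower figure under that rule, with any baseline correlation relied on stated as an assumption.
- It adds that about 64 per arm detects roughly 0.5 SD with 80% power for any single pair, unadjusted and without covariate gain. A non-significant aerobic-versus-combined result will therefore be reported as an estimate with its 95% CI (half-width about 0.35 SD) and not as evidence of equivalence.

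The cost is one paragraph, with no extra patients and no change to trial conduct. If a multiplicity rule is adopted, the quoted power may be less favourable than the present 80%.

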## Monitoring harms

### Adverse events

Study supervisors record any adverse events that occur as a result of the testing or training activities of the study. Participants are also asked to directly report any adverse events they experience. Reported adverse events are recorded by the research staff and reported both to the relevant ethics committee and as relevant in any subsequent publications and reports. Patients who experience an adverse event will be referred to the relevant health professional for a medical assessment. All participants will be covered by the Patient Insurance that is made available for participants in clinical studies at Karolinska University Hospital.

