Group 3 (UC) serves as the control group and receive usual care for breast cancer and general information on physical activity but no supervised exercise training or prescription.

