## Discussion

This study will provide a more complete understanding of the effects of different modalities of exercise on the physical and mental health of breast cancer survivors in the short and long term as well as adding further knowledge regarding the potential exercise may have in managing fatigue, the most commonly reported but poorly understood side-effect of cancer diagnosis and treatment.

There is a concern by some health professionals and researchers, both within and outside of the oncology setting, that high intensity exercise training may not be feasible or safe for individuals with a history of cancer. However, recent controlled trials have adopted high intensity training and showed exercise induced physical adaptations to be superior to low or moderate intensity exercise [18, 36] and concluded that this mode of exercise to be safe and well tolerated in both patients undergoing chemotherapy [18, 37] and cancer survivors [38–40].

The results of the study will be communicated to all participants at the conclusion of the trial. The findings of the study will be shared with the public and research community by way of scientific peer-reviewed publications and presentations at scientific meetings. Popular science articles will be written to inform the public of the study results and study findings will be communicated to the relevant organisations and funding bodies for dissemination to relevant health care and policy professionals.

In terms of advancement of cancer survivor care, we expect that dissemination of the knowledge gained from this study to contribute to developing effective strategies to improve the physical and psychosocial health of breast cancer survivors. In particular, we expect that the knowledge will aid our understanding of the benefits and issues associated with long term exercise programs.

This randomised controlled trial will generate substantial information regarding the effects of different types of exercise on the health of patients with breast cancer undergoing chemotherapy. We anticipate that the results of this study will help to develop future exercise programs and interventions that are more effective and appropriate for and attractive to patients with breast cancer.

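### Adverse events are filtered by attribution and observed far more often in the exercise arms, so a comparison of events between arms would be unreliable

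*Protocol article*

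**What the plan says.** The protocol article, under Adverse events, describes two ways in which an event can enter the record.

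- **Supervisor route:** "Study supervisors record any adverse events that occur as a result of the testing or training activities of the study". The supervisor must first judge that the event was caused by a study activity.
- **Participant route:** "Participants are also asked to directly report any adverse events they experience". This is limited neither by arm nor by cause. Research staff record what is reported, and the events go to the ethics committee and, where relevant, into publications.

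On contact with staff, the section on Phase I states: "Both exercise groups train twice per week on non-consecutive week days for 16 weeks". It adds: "An exercise physiologist or oncology nurse supervises all sessions to ensure safety, correct technique and adherence to the exercise protocols". Usual care, by contrast, receives "general information on physical activity but no supervised exercise training or prescription".

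Testing applies to the whole trial: "Data collection will occur prior to, directly after and at one, two and five years following the completion of the 16-week intervention period". No exemption is given for usual care.

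**The concern.** In women receiving chemotherapy, many events have more than one possible cause. The Background lists cardiovascular complications and increased pain among the problems these patients already face, and strenuous exercise could plausibly bring on or worsen the same problems. Whether one such event resulted from training often cannot be judged in the individual. Randomisation answers that question at group level, but only if events are collected in the same way in each arm before anyone decides on cause.

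The supervisor rule reverses that order. The judgement is made by staff who deliver or oversee the exercise and so know the allocation, and it decides whether the event is recorded by that route at all. Those staff also see exercise participants twice a week, while the article describes no study contact for usual care between baseline and week 16.

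What is at stake is the reading of any adverse-event table by arm. The Discussion reports a worry among some professionals that "high intensity exercise training may not be feasible or safe for individuals with a history of cancer", and both exercise arms include high-intensity intervals. A concurrent randomised control group is well placed to inform that question, and unequal collection weakens it.

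**Working it through.** The article gives no adverse-event rate, margin or power, so there is no figure to reproduce. The check compares the recording routes by arm and then illustrates how unequal capture acts.

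**1. Routes by arm**

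| | Exercise arms | Usual care |
|---|---|---|
| Supervisor route, training events | Yes, if judged caused by training | Not applicable |
| Supervisor route, testing events | Yes, if judged caused by testing | Yes, if judged caused by testing |
| Participant route, any event | Yes | Yes |
| Supervised sessions, baseline to week 16 | 2 per week × 16 weeks = 32 | 0 |
| Common schedule or question for asking | None fixed | None fixed |

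The participant route is open to all arms, but the occasions to use it in person are not equal. The 32 against 0 counts contacts. It does not measure capture.

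**2. More capture in the exercise arms**

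Let *r* be the true risk, equal in both arms, and *s*_ex and *s*_uc the probabilities that an event is captured. Then

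- observed risk difference = *r* × (*s*_ex − *s*_uc)
- observed risk ratio = *s*_ex / *s*_uc

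All values of *r* and *s* below are assumptions. The true difference is 0 throughout.

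| True risk | Capture 0.9 v 0.9 | Capture 0.9 v 0.6 | Capture 0.9 v 0.3 |
|---|---|---|---|
| 10% | 0 points | +3 points | +6 points |
| 20% | 0 points | +6 points | +12 points |
| 30% | 0 points | +9 points | +18 points |
| Risk ratio | 1.0 | 1.5 | 3.0 |

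With the planned 80 per group and a true risk of 20%, capture of 0.9 gives 80 × 0.20 × 0.9 = 14.4 recorded events in an exercise arm. Capture of 0.6 gives 80 × 0.20 × 0.6 = 9.6 in usual care.

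**3. Less capture in the exercise arms**

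Suppose that exercise truly raises the risk from 20% to 30%. Suppose also that events mentioned at sessions are often put down to chemotherapy and go no further, so that capture is 0.6 in exercise and 0.9 in usual care (again assumed). Then

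- exercise: 0.30 × 0.6 = 0.18
- usual care: 0.20 × 0.9 = 0.18

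The observed difference is 0 and the observed ratio 1.0. The true values are +10 points and 0.30 / 0.20 = 1.5. The same collection rules can therefore create a difference or conceal one, and the article gives no means of telling which has happened.

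**4. Equal capture**

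When *s*_ex = *s*_uc, the false difference is 0 and the ratio is correct at any true risk. That is what a common question at common times aims for.

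**The case against.** The strongest reply is the sentence that follows the supervisor rule. Participants are asked about any event, and research staff record what they report. A reader of the supervisor sentence alone might infer that usual care can produce no comparable events, that anything not judged exercise-related is lost, that recorded events in usual care would be near zero, and that net harm therefore cannot be estimated. The documents do not support that reading:

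- The participant route has no limit by arm or cause.
- Usual care is tested too, so testing-related events there qualify even under the supervisor route.
- Symptoms on the MSAS and quality of life on the EORTC QLQ-C30 (Secondary outcomes), and blood counts, co-morbidities, sick leave, recurrence, survival and cause of death (Additional measures), are planned without restriction to an arm. They do not replace an adverse-event record, but they allow randomised comparisons of some harms.

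Two further points have weight. Comparative safety is not among the three stated aims, no between-arm test of adverse events is promised, and the Discussion answers the safety worry with earlier trials that found this kind of exercise well tolerated. Also, an article condenses a full protocol, and the wording and timing of adverse-event questions may be set out there. The absence of that detail is not by itself a fault.

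These replies do not reach the stated rule. The article itself makes causal attribution the condition for supervisor recording, and the contact imbalance follows from the design. The participant route leaves open when and how each arm is asked, so it does not show that capture is equal. The trial intends to publish its adverse events, and readers of a three-arm trial will compare them by arm whether or not a test is planned.

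**Conclusion.** The point holds in a limited form. Recording by supervisors depends on attribution, observation is much denser in the exercise arms (32 planned sessions against 0), and nothing in the article equalises how events are asked for. Ascertainment is therefore likely to differ by arm, and a between-arm comparison of adverse events would be unreliable in either direction.

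The size is unknown. The figures above (false risk ratios of 1.5 to 3.0, false differences of 3 to 18 points, or a true 10-point excess reduced to nothing) rest on assumed risks and capture probabilities and show only how the bias works. Usual care events are not excluded, and a comparison is not impossible. The primary fatigue analysis is unaffected. The change is worth making because the fault lies in a stated collection rule and the remedy is cheap.

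**What to change.** In the Adverse events section, replace the attribution-based rule with wording such as:

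> All adverse events are recorded, whatever their suspected cause. They are asked for with the same standard question in all three arms at each scheduled assessment, at least at week 16. Relation to exercise or testing is recorded separately. Events obtained from this question are tabulated by randomised arm as counts and proportions. Events observed at training sessions are listed separately and are not added to that table.

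If the full protocol already contains such a rule, the article's sentence should be brought into line with it.

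The cost is one standard question at visits that already take place, plus one table by arm. No extra visits or staff are needed. The main downside is that many chemotherapy-related events will be recorded. Recruitment began in March 2013, so women who passed week 16 before the change will not have been asked in this way. The table should state how many in each arm were asked.
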